# Tapering of prescribed opioids in patients with long-term non-malignant pain (TOPIO)—efficacy and effects on pain, pain cognitions, and quality of life: a study protocol for a randomized controlled clinical trial with a 12-month follow-up

**DOI:** 10.1186/s13063-021-05449-5

**Published:** 2021-07-28

**Keywords:** Opioid, Long-term pain, Chronic pain, Prescribed, Tapering, Quality of life, Mental health, Physical health, Functioning, Opioid use disorder

## Abstract

**Background:**

Opioids are still widely prescribed to long-term pain patients although they are no longer recommended for long-term treatments due to poor evidence for long-term efficacy, risks of serious side effects, and the possibility of inducing opioid hyperalgesia. In a Cochrane study from 2017, the authors identified an urgent need for more randomized controlled trials investigating the efficiency and effects of opioid tapering.

The study aimed to assess (1) the efficiency of a structured intervention in causing stable reductions of opioid consumption in a population with long-term non-malignant pain and (2) effects on pain, pain cognitions, physical and mental health, quality of life, and functioning in response to opioid tapering.

**Methods:**

The study is a randomized controlled trial. The sample size was set to a total of 140 individuals after estimation of power and dropout. Participants will be recruited from a population with long-term non-malignant pain who will be randomly allocated to (1) the start of tapering immediately or (2) the control group who return to usual care and will commence tapering of opioids 4 months later. A 12-month follow-up is included.

When all follow-ups are closed, data from the Swedish drug register of the National Board of Health and Welfare will be collected and individual mean daily opioid dose in morphine equivalents will be calculated at three time points: baseline, 4 months, and 12 months after the start of the intervention. At the same time points, participants fill out the following questionnaires: Numeric Pain Rating Scale (NPRS), Tampa Scale of Kinesiophobia (TSK), Pain Catastrophizing Scale (PCS), Chronic Pain Acceptance Questionnaire (CPAQ-8), Hospital Anxiety and Depression Scale (HADS), and RAND-36. At baseline and follow-up, a clinical assessment of opioid use disorder is performed.

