### Trial design {8}

The design of the present study is an RCT, which is under recruitment and conducted among patients with long-term pain who have been accepted to undergo a structured intervention aiming to taper opioid long-term treatments. The study population will be randomly allocated to either (1) the start of tapering opioids immediately or (2) the control group who will return to usual care and commence tapering of opioids 4 months later. A 12-month follow-up after the start of the intervention is included (Fig. 1). The study lies within a superiority framework. Primary endpoints are hypothesized to generate a decrease in opioid use in comparison to controls.

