#### Primary outcomes

Consumption of opioids, measured as MME, will be evaluated using data extracted from the Swedish drug register of the National Board of Health and Welfare (SDPR) where registration of all withdrawals of prescribed drugs is made. MME will be calculated using these data. At all baseline visits and 12-month follow-ups, the MME will be calculated for the preceding 90 days, but at 4 months after the intervention, the dose will be calculated for the preceding 30 days as the intervention is estimated to last approximately 3 months.

Self-reported opioid consumption will also be evaluated and reported in MME. Calculation of morphine equivalent dose will be performed with conversion factors used in Cochrane review [7].

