### Participant timeline {13}

Participants will be enrolled in the trial for 12 months (intervention) or 16 months (control) following baseline assessment. The structured tapering intervention has a 4-month duration, but may be prolonged.

Participants denying tapering, but accepting to participate, will be followed up after 12 months for dropout analysis (Fig. 1).

A SPIRIT diagram (Table 1) is provided detailing the timing of enrolment, interventions, and assessments. Any methodological changes in the study design or sample size that may potentially affect the participants’ safety or study procedures will be discussed in the committee of ethics.

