#### Secondary outcomes

Before a baseline visit, a phone call by a study nurse to orally inform about the trial is made and a questionnaire with secondary outcomes and baseline characteristics is mailed to participants as a part of reporting to SQRP, but with a reduced content for the study population [32]. Participants denying tapering are reported to SQRP only at baseline visits. A fulfilled questionnaire is required to be scheduled at a baseline visit for all participants. The baseline visit must occur within 3 months after the questionnaire has been filled out.

The follow-up questionnaire is sent by mail 1 month before time points: 1 month (all participants), 8 months (controls), and 12 months (all) after the start of tapering.

Twelve months after the start of tapering, a phone call by administration staff is followed by a mailed questionnaire.

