## Statistical methods

### Statistical methods for primary and secondary outcomes {20a}

All statistical analyses will be performed with the SPSS software (version 25, IBM Inc). Continuous data will be expressed by means, standard deviation and 95% confidence interval, and categorical data in numbers and percentages.

The intervention arm (tapering opioids) will be compared with control (waiting list) for primary and secondary outcomes at 4 months of follow-up. Statistical analysis of differences between groups will be performed per protocol (attending follow-up 4 months after the start of the intervention and attending second baseline visit in controls) with a paired *t*-test regarding the primary outcome and a Wilcoxon signed-rank test regarding secondary outcomes.

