### Methods for additional analyses (e.g., subgroup analyses) {20b}

#### Retention to intervention at 12 months

Analysis of retention to the tapered dose will be performed with a paired analysis within the allocated group. Changes in percent from the time point for follow-up after the received intervention at 4 months (intervention) or 8 months (control) will be calculated. The analysis will be performed with repeated measures ANOVA.

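### Outcome times run on two clocks: the questionnaire list, read literally, has nothing due at month 4 in either arm, and the month-4 dose can be taken over different windows in the two arms

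*Protocol article*

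**What the plan says.** **Counted from the start of the intervention or tapering**

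- Abstract, Methods: dose "will be calculated at three time points: baseline, 4 months, and 12 months after the start of the intervention". The questionnaires are tied to the same points.
- Trial design {8}: "A 12-month follow-up after the start of the intervention is included".
- Plans for assessment and collection of outcomes {18a}, secondary outcomes: questionnaires are mailed one month ahead of 1 month (all participants), "8 months (controls), and 12 months (all) after the start of tapering".
- Statistical methods {20a}: the analysis set for the between-arm comparison is defined as "attending follow-up 4 months after the start of the intervention and attending second baseline visit in controls".
- Outcomes {12}, primary outcomes: "but at 4 months after the intervention, the dose will be calculated for the preceding 30 days". The same sentence gives a 90-day window to all baseline visits and to the 12-month follow-up.

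**Counted from baseline, or only interpretable that way**

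- Participant timeline {13}: "Participants will be enrolled in the trial for 12 months (intervention) or 16 months (control) following baseline assessment".
- Retention to intervention at 12 months {20b}: follow-up after the received intervention falls "at 4 months (intervention) or 8 months (control").

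**Linking the two:** Trial design {8} describes controls as "the control group who will return to usual care and commence tapering of opioids 4 months later".

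Two further rules bear on the questionnaires. {18a} requires a completed questionnaire before any baseline visit is booked, and the visit must follow within 3 months of completion. {18b} schedules follow-up visits at 4 and 8 months, where an unreturned questionnaire can be completed, but does not say from which date those months run.

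**The concern.** A randomised comparison should measure both arms at the same time since randomisation. A clock that starts with tapering differs by 4 months between these arms and has no starting point for someone who is allocated but never begins. If site staff follow {18a} as printed, no month-4 questionnaire is due in either arm.

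That matters beyond the secondary outcomes. Objectives {7} places non-inferiority on pain, pain cognitions, health, quality of life and functioning inside the primary objective. The untreated control values needed for it exist only at the end of the wait.

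For dose, the anchors are a post-randomisation event in one arm and attendance at a visit in the other, and the averaging window depends on what that visit is called.

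**Working it through.** **The plan's own figure.** With d = 0.5, 80% power, α = 0.05 (two-sided assumed) and 10% drop-off: n = 2(1.96 + 0.842)²/0.5² = 62.8, so 63 per arm, and 63/0.90 = 70. The stated 70 per group is reproduced, and the timing question does not affect it.

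**Conversion to one clock.** Months since randomisation = months since taper start + 0 (intervention) or + 4 (controls, from {8}).

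| Source, read literally | Intervention | Controls |
|---|---|---|
| Abstract: 4 and 12 after start | 4, 12 | 8, 16 |
| {18a}: 1 (all), 8 (controls), 12 (all) after start of tapering | due 1, 12 (mailed 0, 11) | due 5, 12, 16 (mailed 4, 11, 15) |
| {13}: end of enrolment, from baseline | 12 | 16 |
| {20b}: follow-up after the received intervention | 4 | 8 |
| {20a}: between-arm comparison | 4 months after start | second baseline visit, about 4 |

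Three things follow.

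1. The controls' 8 months is month 12 since randomisation in {18a} but month 8 in {20b}. Only the second fits a 4-month wait plus a 4-month intervention.
2. The 1-month entry in {18a} matches no other section. If it is read as 4 months, and the first two entries are counted from baseline, the list gives month 4 in both arms, month 8 in controls, and months 12 and 16 at the end. That agrees with {13}, {18b}, {20a} and {20b}.
3. An end-of-wait control questionnaire can be inferred from the baseline-visit rule, but that rule allows completion up to 3 months before the visit. For a visit at month 4, the value could date from month 4 − 3 = 1.

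**Dose window.** At the comparison the intervention arm has 30 days. Controls are at a baseline visit, so the 90-day rule can apply to them. In a control on a stable dose the two windows agree; they differ if the dose drifts during the wait. The choice is not neutral where dose is changing. Take a weekly-step taper of a fixed share of starting dose, begun at randomisation, with the first week at full dose and the measurement at day 120:

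| Pace per week ({11a} advises 5–10%) | Mean over last 30 days | Mean over last 90 days |
|---|---|---|
| 5% | 27.5% of starting dose | 48.9% |
| 7.5% | 0.9% | 26.6% |
| 10% | 0% | 15.0% |

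This illustrates sensitivity to the window. It does not estimate bias, since {12} assigns 30 days to the tapering arm.

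**Delay to taper start.** None is stated. For an assumed delay of 1 to 4 weeks in the same model, the 30-day dose at day 120 after randomisation exceeds the no-delay value by 5 to 20 points of starting dose at 5% per week, about 6 to 24 at 6%, and 0 to 3 at 10%. Measuring from taper start leaves this difference out. With no delay, the difference is zero.

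**The case against.** The strongest reply is that the randomised comparison is in fact located. {20a} compares the arms at 4 months, with controls at the second baseline visit. The intervention arm starts immediately ({8}): the envelope is opened at the baseline visit ({16c}) and the treatment plan is made there ({11a}). Start and randomisation therefore nearly coincide by design. The 12-month analysis is within group ({20b}), so months 12 and 16 are never set against each other. Timing post-taper follow-up from taper start is ordinary in a wait-list trial. Register dose is retrieved for those who discontinue or deviate ({18b}).

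All of this stands, and it rules out several stronger readings that a reader might infer:

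- **The arms have no common time zero.** {20a} shows an intended comparison at about month 4 in both.
- **Controls have no end-of-wait questionnaire.** That is true only of the list in {18a}. The baseline-visit rule and the 4-month visit in {18b} imply one, and Fig. 1 and Table 1 are not shown and may list it.
- **Both arms would be compared after tapering, with an expected difference near zero.** {20a} excludes this by using the second baseline visit.
- **A delay shifts dose by up to 40 points (4 weeks × 10%).** At 10% per week the taper is over by week 10, before the 30-day window opens, and a 4-week delay then moves the mean by only about 3 points.

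The reply does not repair the list in {18a}, the window rule in {12}, or the lack of a calculation date for an allocated participant who never starts. Register data exist for that person, but the start-based clock does not say when to compute the dose.

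**Conclusion.** The concern holds as an inconsistency that should be corrected. The stated time points cannot all be followed. Read literally, {18a} yields no month-4 questionnaire in either arm; the 30-day and 90-day windows can meet at the primary comparison; and never-starters have data without a defined date.

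The randomised design itself is not undermined, because the intended comparison at about month 4 is clear from {20a}. No bias can be quantified: the delay to taper start is not stated and may be near zero, so the figures above for 1 to 4 weeks are assumptions. The finding rests on the text alone, and the unseen figure and schedule table could resolve the questionnaire part.

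**What to change.** 1. In the Abstract, {12}, {18a} and {20a}, count all time points from the date of randomisation.
2. Calculate the month-4 register dose in one identical, fixed day window after randomisation for every allocated participant in both arms, whatever the visit date and whether or not tapering began. State that the 90-day baseline rule does not apply to controls at this point.
3. Correct the list in {18a}, including the 1-month entry: month 4 in both arms, completed in controls near the end of the wait and before tapering begins; then month 12 (intervention) and months 8 and 16 (controls). Say in {18b} that the 4- and 8-month visits are counted from randomisation.

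The cost is protocol wording and a corrected mailing list. Dispensings are dated and extracted only after all follow-ups close ({18a}), so the dose window can be set for everyone. With 62 of 140 allocated at the time of the article, the questionnaire timing can be made explicit for the remaining 78. The one downside is that a late starter's month-4 dose will look slightly less favourable to tapering.

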**Discussion:**

A better understanding of the efficiency and effects of opioid tapering could possibly facilitate attempts to taper opioid treatments, which might prove beneficial for both the individual and society.

**Trial registration:**

ClinicalTrials.gov NCT03485430. Retrospectively registered on 26 March 2018, first release date. “Tapering of Long-term Opioid Therapy in Chronic Pain Population. RCT with 12 Months Follow up (TOPIO).” First patient in trial 22 March 2018.

## Administrative information

**Table Taba:** 

Title	Tapering of prescribed opioids in patients with long-term non-malignant pain (TOPIO) – Efficacy and effects on pain, pain cognitions, and quality of life: a study protocol for a randomized controlled clinical trial with a twelve-month follow-up	
Trial registration {2a and 2b}.	Registered in Clinicaltrials.gov with id: NCT03485430, “Tapering of Long-term Opioid Therapy in Chronic Pain Population. RCT with 12 Months Follow up (TOPIO)”. First release date: 26/03/2018, retrospectively registered. First patient in trial 22/03/2018. https://clinicaltrials.gov/ct2/show/NCT03485430.	
Protocol version {3}	Record log in Clinical Trials:	
	06/22/2021	Author’s comment: Collaborating Centers in Gothenburg and Linkoeping are added as intervention expands to a multi-center trial. These centers will be recruiting participants and performing intervention with start autumn 2021. As no inpatient tapering has been performed since trial start this way of conducting intervention is no longer permitted.
	09/01/2020	Author’s comment: Acronym added to title. Exclusion criteria more thoroughly described but has been the same since start in March 2018. The trial has only recruited patients with prescribed opioids and not recruited participants with illicit drug use.
	05/07/2020 09:16 ClinicalTrials.gov	PRS Review comments recorded. Listed each Outcome Measure separately, using “Add a __ Outcome Measure” feature, please use/keep this format for future records. ClinicalTrials.gov QA9
	05/06/2020 05:54	New power-calculation has been performed January 2020. Study period is prolonged due to this. Outcome measurements has been more thoroughly described in this last entry. Data-collection has been the same since start in March 2018.
	03/30/2018 14:18 ClinicalTrials.gov	Made minor editorial changes (e.g., spelling, grammar, punctuation). ClinicalTrials.gov QA37
Funding {4}c	Lund University Hospital, Lund University, Southern Healthcare Region and Greta and Johan Kock’s Foundation.	

## Introduction

### Background and rationale {6a}

In 1986, a study including 38 patients with long-term non-malignant pain concluded that opioids could be prescribed safely on a long-term basis [1]. Despite low-quality evidence, the paper was widely cited and greatly influenced prescription patterns for patients with long-term pain. Opioid use increased gradually, and in 1996, the rate of opioid use began accelerating rapidly after the introduction of oxycodone [2, 3]. An opioid epidemic has later been described in the USA caused by rises in opioid prescription use but also social determinants, e.g., lack of education [4]. It imposes a major threat to public health with a dramatic threefold increase in opioid overdose deaths from 1999 to 2017 [5].

Further studies have not been able to establish advantages of opioid treatments exceeding 3 months for long-term pain but rather pointing out disadvantages with long-term opioid therapy [6, 7]. A Cochrane review of opioids for pain associated with rheumatoid arthritis found limited evidence for the efficacy of weak opioids up to 6 weeks and no evidence beyond 6 weeks [8]. In lumbago, evidence indicates a short-term effect on pain if the treatment continued for less than 8 weeks though not proven more efficacious than NSAID. Opioid treatment was, however, associated with worse prognosis for return to work [9]. In this context, it is interesting to note publicly available information from the Swedish National Board of Health and Welfare displaying prescription patterns of individuals applying for sick leave. In this report, 42% of patients with the diagnosis of lumbago were prescribed opioids before sick leave with an increase to 70% after the initiation of sick leave [10]. In Sweden, opioids do not, however, constitute a problem of equal magnitude as in the USA. Information made accessible by the Swedish National Board of Health and Welfare indicates a stable prescription rate with a tendency toward a slight decrease in the number of individuals receiving opioid dispensation from 10.2% in 2006 to 9.38% in 2015 [11].

Thus, increasingly emphasized by clinical guidelines and strategic document, long-term opioid treatments are not considered evidence-based practice [6, 12, 13]. The International Association for the Study of Pain (IASP) has in a statement 2018 recommended caution when prescribing opioids for long-term pain and concluded that preferred treatment strategies are interventions that aim at improving the quality of life, especially those integrating behavioral and physical treatments [14]. Besides not been proven efficacious in the treatment of long-term pain, opioid treatments can also lead to serious side effects such as addiction, overdose, and death by overdose. Less dramatic but more frequent side effects are constipation, nausea, sedation, and increased risk of falls and fractures. Depression and sexual dysfunction may also develop over time. In addition, cognitive side effects are prevalent in populations receiving long-term opioid therapy [6, 7, 15, 16].

Side effects of long-term opioid medication can thus hamper both physical and mental health as well as function. Moreover, the phenomenon opioid-induced hyperalgesia has generated increasing attention [17–20]. Opioid-induced hyperalgesia is defined as a heightened state of nociceptive sensitization instigated by the exposure of opioids, which leads to the paradoxical effect whereby a patient receiving opioids for the treatment of pain can become more sensitive to painful stimuli. Opioid-induced hyperalgesia could thus possibly explain the loss of opioid efficacy in some patients.

To sum up, there are good reasons to be careful when prescribing opioids for long-term pain due to poor evidence for long-term efficacy, risks for serious side effects, addiction, negative impact on return to work, and, finally, the possibility of inducing hyperalgesia by the very exposure of opioids. Nevertheless, it can be challenging to help patients taper and end their opioid treatment. Both clinicians and patients may struggle with beliefs that might hamper the process. Qualitative data points to challenges in patients’ beliefs such as the fear of increased pain with opioid tapering [21, 22]. Clinicians, on the other hand, predict negative reactions from patients upon a recommendation to reduce opioid intake, varying from resistance to change to becoming overtly angry. Consultations entailing discussion of opioid tapering are by some clinicians described as emotionally charged, exhausting, and even threatening [23, 24]. Both patients’ and clinicians’ beliefs might thus constitute barriers for successful change in opioid prescriptions. The communication about tapering is facilitated if patients understand their individualized reasons for tapering, are encouraged to have input into the process, and are assured they will not be abandoned [25]. Patients with opioid tapering experience identified social support and a trusted health care provider as facilitating factors for their process [21]. There are guidelines on how to taper opioids with practical advice where tapering of the long-term treatment is described as a method to determine the benefit–harm ratio for the individual patient [26, 27]. An improved research-based understanding on what patients can expect when entering an opioid tapering program could very possibly be helpful in this demanding clinical situation.

A Cochrane systematic review conducted in 2017 attempted to investigate the effectiveness of different methods to taper prescribed opioids [28]. The authors concluded that there was no evidence for the efficacy or safety of methods for reducing prescribed opioid use in long-term pain. They found only five randomized controlled trials (RCTs), the designs were too heterogeneous to allow for a meta-analysis, and the findings were mixed. The authors saw a vital need for more RCTs that focus on opioid medication use in patients with long-term pain with reduction of opioid dose as a primary clinical goal together with measures of patient-reported outcomes of pain, mood, and functioning. The present RCT is thus designed to meet these requirements in order to be beneficial for patients, clinicians, and researchers.

